## Methods

### Study design

The study was designed as a pragmatic, multi-site, randomized controlled trial of the 'Don't Panic' course versus a wait-list control group. Measurements were taken at baseline measurement (T0) followed by a posttest measurement after three months (T1). To monitor effect maintenance over time, the experimental group underwent a prolonged follow-up measurement nine months after baseline, i.e., six months after the end of the intervention (T2). The study was designed to mimic the Dutch health care system as naturalistically as possible in terms of patient recruitment and the manner in which intake, offering the intervention, and monitoring outcomes are conducted. This was done to enhance external validity. The randomization took place after administration of the International Neuropsychiatric Interview Plus (MINI-Plus; [24]), and was carried out centrally by an independent third party. A blocked randomization scheme was used, stratified by mental health centre, subthreshold PD versus mild PD, and by presence versus absence of co-occurring agoraphobia. The latter was included because it was assumed that agoraphobia may be a prognostically relevant factor for outcome in PD. This procedure ensures that participants with and without PD or agoraphobia were equally distributed across both trial arms. See Figure 1 for participants' flow through the study. The trial protocol was approved by an independent medical ethics committee (METIGG).

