### Sample size

Power analysis indicated that 129 participants per condition are required in order to detect a difference in symptom reduction, equivalent to a standardized effect size of at least 0.35 in a two-sided test at alpha = 0.05 and a power of (1-beta) = 0.80.

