### Analyses

All analyses were conducted in agreement with the intention to treat principle [56], hence all participants were analyzed in the condition to which they were randomized, and missing endpoints at follow-up were imputed using a regression model with the best available predictors of outcome and the best predictors for dropout. The first set of predictors is required to get the most precise estimates for the missing values; the latter to correct for bias that may stem from differential loss-to-follow-up associated with T0 variables [57].

In all analyses on effectiveness, we controlled for the clustering of data caused by the multi-site character of the study. Clustering violates the assumption of independence of observations, and may thus affect standard errors and *P *values. So-called 'robust standard errors' and correct *P *values were obtained using the first-order Taylor series linearization method. All analyses were conducted with Stata 9.0 [58].

For the primary outcome on PDSS-SR, a Gaussian regression model was used to test the hypothesis of superior intervention effects in the experimental arm compared to the waitlist control group. We calculated between-group effect sizes at posttest by subtracting the mean posttest score of each condition and dividing the difference by the pooled standard deviation (Cohen's *d*). In the field of psychological interventions, effect sizes in the range of 0.00 to 0.32 are regarded as small, while effect sizes of 0.33 to 0.55 are moderate, and effect sizes of 0.56 to 1.2 are large [59].

As primary outcome we also compared the proportion of participants manifesting a clinically significant change on the PDSS-SR (responders) across the two groups. Clinically significant change was defined according to the criteria proposed by Jacobson and Truax [60]: a change should move from a dysfunctional distribution to a functional one, and the change should be statistically reliable in the sense that the observed change cannot be put down to measurement error in the PDSS-SR. Because we studied a population with subthreshold and mild PD, we considered scores below one standard deviation of the mean pretest score on the PDSS-SR as falling within the functional range [61]. This binary outcome was then used to obtain the odds ratio (OR) using a logistic regression of the binary outcome on the intervention dummy and the numbers-to-be-treated (NNT) using Gaussian regression.

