The sample can be divided in two groups: people with relatively mild manifestations of MINI-DSM-IV panic disorder and those with subthreshold manifestations not meeting the diagnostic criteria. When we focus on the latter group: people at risk of developing panic disorder, we can look at how many of these persons developed PD meeting the diagnostic criteria of the DSM-IV at T1. When we pay attention to the group with mild PD, we can see how many of these persons became PD-free at T1. For the primary outcome on the MINI-Plus we compared the proportion of success across the two groups. Success was defined as: (a) the participant had no PD at T0 and stayed PD free at T1 or (b) the participant had mild PD at T0 and no PD at T1. This yields a binary outcome where failure is coded 0, and success is coded 1. In a next step, this binary outcome was used to obtain the OR and the NNT.

The demographic and clinical characteristics of responders versus non-responders, and success versus failure, were compared using Student's *t *test for independent groups or Pearson's chi-squared tests when appropriate.

For the secondary outcomes on continuous measurement scales, a Gaussian regression model was used to test the hypothesis of superior intervention effects in the experimental arm compared to the wait-list control group. Furthermore, the between-group effect sizes (Cohen's *d*) were calculated. To test the maintenance of the effects at six-month follow-up we used a paired-samples t test to analyze the difference in mean score of the self-report measures in the experimental group from T0 to T1, T0 to T2 and T1 to T2.

To provide a more comprehensive picture of the effects of the intervention, results for the outcomes will also be presented for completers only (defined as participants who attended at least six sessions).

The following variables will be examined as potential mediators: cognitive aspects of panic disorder, symptoms of agoraphobia, anxiety and mastery. Furthermore, potential moderating variables (e.g., socio-demographic characteristics, panic disorder, agoraphobia, treatment credibility and mastery) will be analyzed.

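### The responder model contains treatment arm alone, and no stated effectiveness model uses T0 PDSS-SR, PD status or agoraphobia, so available precision is forgone

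*Protocol article*

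**What the plan says.** **Design.** Under Study design: "A blocked randomization scheme was used, stratified by mental health centre, subthreshold PD versus mild PD, and by presence versus absence of co-occurring agoraphobia". The article justifies agoraphobia as a stratum by its assumed prognostic relevance. Table 1 (Instruments) shows PDSS-SR at T0, T1 and T2.

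**Sample size.** The article states that "129 participants per condition are required in order to detect a difference in symptom reduction". It sets the standardised effect at 0.35 or more, with two-sided alpha 0.05 and power 0.80.

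**Analyses.** Four statements bear on the point:
- Continuous PDSS-SR is tested with a Gaussian regression model whose covariates are not given. Cohen's d is then defined by "subtracting the mean posttest score of each condition and dividing the difference by the pooled standard deviation".
- PDSS-SR responders are compared by "a logistic regression of the binary outcome on the intervention dummy", with no other term named. The NNT comes from a Gaussian regression.
- MINI-Plus success means either no PD at T0 and still none at T1, or "the participant had mild PD at T0 and no PD at T1". An OR and an NNT follow; the model terms are not given.
- Site clustering is handled in all effectiveness analyses by robust standard errors from Taylor linearisation.

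T0 variables otherwise appear as predictors for imputation, as possible predictors of outcome, in comparisons of responders with non-responders, and as mediators or moderators. PD and agoraphobia are on the moderator list.

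**The concern.** The trial stratifies on two clinical factors and collects the baseline value of its main outcome, then writes out a primary responder model with none of them and an effect size from raw posttest means. Two things are at stake.

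The first is precision. A baseline score that correlates with the posttest score removes residual variance at no cost in participants. Leaving out prognostic stratification factors also makes the usual standard errors too large on average, so inference is conservative.

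The second is interpretation of the odds ratios. Both branches of the MINI-Plus success definition reduce to having no PD at T1, so T0 PD status is an obvious candidate predictor. An OR that ignores PD status and one conditional on it are different quantities, and the article does not say which is meant.

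**Working it through.** **Step 1: reproduce the stated size.** Inputs from Sample size: d = 0.35, two-sided alpha 0.05, power 0.80.

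n per arm = 2 × (1.960 + 0.842)² / 0.35² = 2 × 7.849 / 0.1225 = 128.1, rounded up to 129.

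Power at 129 = Φ(0.35 / √(2/129) − 1.96) = Φ(2.811 − 1.96) = 0.803.

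The figure reproduces as an unadjusted comparison of two means. (With the noncentral t, power at 129 is 0.7997 and 130 are needed, which is immaterial.) The calculation takes no credit for baseline.

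**Step 2: adjust for T0 PDSS-SR.** With T0-T1 correlation r, the residual SD is multiplied by √(1 − r²), so power = Φ(2.811 / √(1 − r²) − 1.96). The article gives no r; every value below is an assumption.

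| assumed r | √(1 − r²) | power at 129 per arm | n per arm for 0.80 |
|---|---|---|---|
| 0 (unadjusted) | 1.000 | 0.803 | 129 |
| 0.2 | 0.980 | 0.818 | 124 |
| 0.3 | 0.954 | 0.838 | 117 |
| 0.5 | 0.866 | 0.901 | 97 |

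At r = 0.5, adjustment is worth 129 / 0.75 = 172 per arm unadjusted. Study sample restricts entry to PDSS-SR below 13 on a 0 to 28 scale, and such range restriction tends to lower r, so the upper rows should not be taken for granted.

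**Step 3: marginal against conditional OR for MINI-Plus success.** The article gives neither stratum success rates nor the share with mild PD, so both are assumed. Take half mild PD and a within-stratum OR of 2.0.

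- *PD status strongly predictive* (control success 0.90 subthreshold, 0.30 mild). Intervention success is 18/19 = 0.947 and 0.857/1.857 = 0.462. Pooled: 0.600 against 0.704. Marginal OR = (0.704/0.296) / (0.600/0.400) = 1.59.
- *PD status weakly predictive* (0.80 and 0.60). Intervention success is 8/9 = 0.889 and 3/4 = 0.750. Pooled: 0.700 against 0.819. Marginal OR = 1.95.

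Wald power at 129 per arm uses log(OR) / SE − 1.96. The unadjusted SE comes from the pooled proportions, and the adjusted SE from the sum of the two strata's information.

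| control success, subthreshold/mild | conditional OR | marginal OR, 25-75% mild | power unadjusted, 50% mild | power adjusted, 50% mild |
|---|---|---|---|---|
| 0.90/0.30 | 2.0 | 1.58-1.71 | 0.42 | 0.57 |
| 0.80/0.60 | 2.0 | 1.95-1.96 | 0.61 | 0.62 |

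For a conditional OR of 3.0 the marginal ranges are 2.11-2.40 and 2.88-2.92. The effect of adjustment therefore runs from substantial to negligible, depending on how strongly T0 PD status predicts success.

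**The case against.** The strongest reply is that most of the model content is simply unstated. The sentence on posttest means defines a descriptive effect size, not the test. The Gaussian model may well include baseline, and an article may leave covariate lists to a fuller document. The treatment-only wording belongs to the responder outcome and cannot be carried over to MINI-Plus. This stands: a reader might infer that every primary analysis is unadjusted, but the article shows it only for the responder model.

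Several further replies also hold:
- Not all strata are ignored: centre enters through the robust standard errors. Nor is baseline absent from the responder outcome, because reliable change is computed from the T0 score.
- A reader might infer that an unadjusted OR is biased toward 1. It is not. It is a valid marginal OR, the test of no effect remains valid, and the gap from the conditional OR is non-collapsibility. The unadjusted risk difference already targets the marginal quantity that an NNT needs.
- A reader might see a contradiction between powering on "a difference in symptom reduction" and reporting a posttest difference. Under randomisation the two between-arm differences have the same expectation, so the wording alone does not establish one.
- Analyses already describes looking at new PD among subthreshold participants and at remission among those with mild PD, and foresees moderator analyses. It would be unfair to say that the article hides the two questions behind one pooled figure.
- The planned power is met without adjustment, and the size of any gain rests on assumed values.

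What the reply does not remove is that one primary model is written without covariates, and that three collected baseline variables, two of them randomisation strata, appear in no stated effectiveness model.

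**Conclusion.** The point holds as an inexpensive improvement, not as a fault in the plan's arithmetic or in the validity of its tests. For continuous PDSS-SR, if the unstated covariates do not include the T0 score, the power forgone at 129 per arm and d = 0.35 is about 0.02 at r = 0.2, 0.04 at r = 0.3 and 0.10 at r = 0.5. For MINI-Plus success, the difference between unadjusted and PD-adjusted analysis ranges from negligible to substantial across the assumed success rates. The correlation, success rates and share of mild PD are all assumptions. The calculations ignore dropout and clustering.

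**What to change.** - Analyse T1 PDSS-SR by regression on arm, T0 PDSS-SR, baseline PD status and agoraphobia, keep the present handling of centre, and report the adjusted mean difference as the primary estimate.
- Keep the pooled posttest SD for Cohen's d. The T0 SD is not a good substitute, because the entry ceiling truncates it and would tend to inflate d.
- Add PD status and agoraphobia to the responder and MINI-Plus logistic models, and label the resulting ORs as conditional.
- Derive each NNT from a standardised (marginal) risk difference based on the same model.
- Report MINI-Plus success by baseline PD stratum next to the pooled result, as Analyses already foresees.

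The cost is a few lines of analysis text; no data or participants are added. The one drawback is that conditional ORs are not directly comparable with unadjusted ones, so the marginal risk difference must accompany them.

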Studies on prevention and early intervention in anxiety disorders indicate that prevention of anxiety disorders through cognitive-behavioural interventions can be successful [17-19]. Only a few studies have been conducted in this field. Gardenswartz and Craske [20] tested a prevention program for panic disorder. Participants consisted of college students who had experienced a panic attack in the last 12 months and had at least moderate anxiety sensitivity (ASI score of 16 or higher; [21]), but did not meet the criteria for panic disorder (CIDI; [22]). They were randomly assigned to either a one-day prevention workshop (n = 55) or a wait-list control (n = 66). The one-day (five-hour) workshop entailed psycho-education, breathing retraining, cognitive restructuring, interoceptive exposure and 'in vivo' exposure. At six-month follow-up nine participants (13.6%) from the wait-list group and only one participant (1.8%) from the workshop group had developed panic disorder, indicating a favourable treatment response.

In a study by Swinson, Soulios, Cox, and Kuch [23], 33 adults with panic attacks seen in two emergency rooms were randomly assigned to groups receiving reassurance (n = 16) or exposure instruction (n = 17). Subjects who had received the exposure instruction significantly improved over the six-month follow-up period for symptoms of depression, avoidance, and panic frequency, whereas subjects receiving reassurance did not improve for any of these variables.

Despite methodological limitations, such as limited generalizability, small sample size and short follow-up periods, the results of these studies suggest that prevention of panic disorder is a promising option.

The aim of this study is to examine the effectiveness of an early intervention for panic symptoms in a sample of self-referred people presenting with subthreshold or mild PD in a randomized controlled trial. We predict that the intervention will show superior effects in reducing panic disorder symptomatology, compared to a waitlisted control group. Furthermore, an economic analysis will be performed to assess the cost-effectiveness of the intervention.

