We recognize a number of limitations in this study. First, because of the absence of a placebo control, it is not clear whether nonspecific components of the intervention, such as social cohesion and expectation of gain contribute to the possible early intervention effect. Future research should use placebo controlled designs to overcome this problem. Secondly, the time available to study a change in PD status was only three months. For ethical reasons the control group received the intervention a few weeks after T1. For future research to study a change in PD status an extended period is advised. Thirdly, because of financial limitations we could not raise the sample size, so the change of protocol by including mild PD caused a lack of power to analyze a reduction of incidence of PD according to the MINI-Plus. Fourthly, there is no control condition at six-month follow-up after the course. Therefore, definite conclusions that the possible effects at six-month follow-up may be related to the intervention are not allowed. Finally, the extended follow-up period was only six months following the conclusion of the course, but longer follow-up periods are needed to know how long the possible effects will persist.

Notwithstanding the limitations, the development and research of an early intervention in panic disorder – a severe and persistent mental disorder, associated with a large burden of disease and extensive economic costs – is of the utmost importance.

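### The MINI-Plus 'success' endpoint pools staying PD-free with remission and is summarised by one OR and one NNT with no stated term for PD status at T0

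*Protocol article*

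**What the plan says.** All of this is in the protocol article.

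- **Endpoint (Analyses).** The primary MINI-Plus outcome is binary, with two limbs. The limb for subthreshold participants reads "Success was defined as: (a) the participant had no PD at T0 and stayed PD free at T1". The limb for those who start with the diagnosis reads "b) the participant had mild PD at T0 and no PD at T1".
- **Effect measures (Analyses).** "this binary outcome was used to obtain the OR and the NNT". No model is named at that point. The one binary model that is described, for the PDSS-SR responder outcome, is "a logistic regression of the binary outcome on the intervention dummy".
- **The two subgroups (Analyses).** For the subthreshold group, "we can look at how many of these persons developed PD meeting the diagnostic criteria of the DSM-IV at T1". The mild PD group gets a matching sentence about becoming PD-free. Both are worded as counts, with no OR, NNT or test attached.
- **Descriptive comparison (Analyses).** "The demographic and clinical characteristics of responders versus non-responders, and success versus failure, were compared using" t tests or chi-squared tests. No division by T0 PD status is stated.
- **Randomisation (Study design).** It was stratified by centre, by subthreshold versus mild PD, and by agoraphobia.
- **Limitations (Strengths and limitations).** The authors state that "the change of protocol by including mild PD caused a lack of power to analyze a reduction of incidence of PD".

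**The concern.** The two limbs of the definition cover two different transitions. A subthreshold participant succeeds unless PD begins within three months. A mild PD participant succeeds only if the diagnosis is lost. The chance of success without the course should therefore differ greatly between the strata.

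Three things follow.

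1. An OR from a model with the intervention dummy alone leaves out a strong prognostic factor that the design itself used as a stratum. It will tend to sit closer to 1 than the effect within strata.
2. One NNT across both strata is a weighted result. It is neither the number treated per onset avoided nor the number treated per remission gained, and a pooled benefit that comes entirely from remission could be misread as prevention of onset.
3. If most failures are people who had PD at T0, anything correlated with PD at T0 will separate successes from failures, whether or not it says who does well.

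**Working it through.** **The plan's own figure.** For d = 0.35, two-sided alpha 0.05 and power 0.80, n = 2 × (1.960 + 0.842)² / 0.35² = 128.1, so 129 per condition. The stated figure reproduces, but it concerns symptom reduction. The article gives no size or power for the MINI-Plus endpoint.

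**Inputs.** The only onset rates in the article are those of the cited prevention study in Background: "At six-month follow-up nine participants (13.6%) from the wait-list group and only one participant (1.8%) from the workshop group had developed panic disorder". Halving them for three months gives 6.8% and 0.9%. A constant hazard gives nearly the same: 1 − (1 − 9/66)^0.5 = 7.1% and 1 − (1 − 1/55)^0.5 = 0.9%. The article gives neither the share with PD at T0 (w) nor remission rates. I assume w from 0.2 to 0.8 and, unless stated otherwise, remission of 30% on the waitlist and 50% with the course.

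**Formulas.** In each arm, pooled success = (1 − w)(1 − onset) + w × remission. NNT = 1 / (difference in success). OR = ratio of the odds of success.

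**A. Effects in both strata.** Staying PD-free: NNT = 1/(0.068 − 0.009) = 16.9; OR = (0.991/0.009)/(0.932/0.068) = 8.0. Remission: NNT = 1/(0.50 − 0.30) = 5.0; OR = (0.5/0.5)/(0.3/0.7) = 2.3.

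| w | Success, waitlist | Success, course | Pooled OR | Pooled NNT |
|---|---|---|---|---|
| 0.2 | 0.806 | 0.893 | 2.01 | 11.5 |
| 0.5 | 0.616 | 0.746 | 1.83 | 7.7 |
| 0.8 | 0.426 | 0.598 | 2.00 | 5.8 |

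The effects within strata are fixed, yet the NNT halves across the range of w. Here the pooled OR lies below both stratum ORs. That is not a general rule when the stratum ORs differ: with the six-month onset rates unscaled (13.6% v 1.8%) and w = 0.2, the pooled OR is 2.56, against 8.6 and 2.3.

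**B. The same OR of 2.5 in both strata.** This isolates the dilution. Success on the waitlist is set at 93% (subthreshold) and 30% (mild PD). With the course these become 97.1% and 51.7%, so the stratum NNTs are 24.5 and 4.6. The unadjusted pooled OR is 1.79, 1.82 and 2.09 at w = 0.2, 0.5 and 0.8, and the pooled NNT is 13.1, 7.8 and 5.5. The true within-stratum OR is 2.5 throughout.

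**C. No effect on onset.** With onset at 7% in both arms and remission at 30% v 50%, the pooled OR is 1.32, 1.57 and 1.91 and the NNT is 25, 10 and 6.2 at w = 0.2, 0.5 and 0.8. A favourable pooled result is therefore compatible with no prevention at all.

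**D. Successes versus failures.** Share of failures with PD at T0 = w(1 − rem) / [w(1 − rem) + (1 − w) × onset]. The share of successes uses rem and (1 − onset) instead. Averaging over arms and taking onset as 4%:

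| w | Remission | PD at T0 among failures | PD at T0 among successes |
|---|---|---|---|
| 0.3 | 50% | 84% | 18% |
| 0.3 | 30% | 88% | 12% |
| 0.5 | 50% | 93% | 34% |
| 0.7 | 50% | 97% | 55% |
| 0.7 | 30% | 98% | 42% |

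At 4% onset and 50% remission, the OR linking PD at T0 to failure is (0.5/0.5)/(0.04/0.96) = 24. The pattern weakens when onset and remission are higher or w is small. Onset 7.7%, remission 70% and w = 0.2 give a 49% share of failures (OR 5.1). Onset 15% and remission 80% give an OR of 1.4, with 57% of failures at w = 0.5 and 25% at w = 0.2.

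**The case against.** The strongest reply is that the endpoint is coherent. It equals no PD at T1, randomisation was stratified on T0 PD, and the comparison asks whether the course raises the PD-free proportion among the people it is offered to. The mix is not an accident either, because mild PD was included deliberately for external validity. Any NNT in a heterogeneous sample depends on case mix. This stands. A reader might infer that the pooled OR and NNT are invalid or answer no question, and the document does not support that.

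A reader might also infer that the trial sets out to test prevention and then fails to do so. The Abstract gives prevention of onset as an aim of the course. The stated purpose of the trial, there and in the Discussion, is to reduce panic disorder symptomatology. Nowhere does the article plan a prevention claim from the pooled OR, and it admits low power for incidence.

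The separate questions are not ignored. The two groups are described, and panic disorder is a listed potential moderator. But the moderator list is tied to no particular outcome, and neither statement attaches an effect measure to a stratum or puts T0 PD in the model for this endpoint. A condensed article may leave stratum tables to a fuller plan. What it does state for a primary outcome is one OR and one NNT from the pooled variable.

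Finally, it is tempting to say that success versus failure simply re-identifies who had PD at T0. That holds only under assumed rates, as D shows. It concerns the descriptive comparison alone and does not touch the comparison between arms.

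**Conclusion.** The point holds in a limited form. The pooled arm comparison is valid, but its stated summary is weaker and less readable than the design allows. Under the assumptions above, a within-stratum OR of 2.5 appears as 1.8 to 2.1 when T0 PD is left out. The pooled NNT moves from 11.5 to 5.8 with the mix and cannot be read as an NNT for onset (16.9) or for remission (5.0). The success-versus-failure comparison is likely to reflect largely T0 PD status if three-month onset is low and remission moderate.

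The sizes rest on an assumed T0 PD share, assumed remission rates, and onset rates scaled from a study of college students given a one-day workshop. The dependence of the NNT on the mix does not rest on those values, provided the absolute effect differs between strata. The dilution of the OR needs only that T0 PD is prognostic and omitted from the model. That the model for this endpoint has the intervention dummy alone is itself read across from the responder outcome, since no model is named for success.

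**What to change.** 1. Keep PD-free at T1 as the pooled endpoint, and adjust or stratify its analysis for T0 PD status.
2. Report the risk difference, OR and NNT with confidence intervals separately for mild PD (remission) and subthreshold PD (onset). Mark the onset result as underpowered, in line with the limitation the authors already state.
3. Label the pooled NNT as specific to the sample's mix, and draw no conclusion about onset prevention from it. It need not be dropped.
4. Compare successes with failures within T0 PD strata, or adjust that comparison for T0 PD.

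The cost is analysis wording only: the stratum was recorded at randomisation and no new data are needed. The downside is wider intervals within strata. With 129 per arm and half the sample in each stratum, power is about 0.41 for onset of 6.8% v 0.9% and 0.64 for remission of 30% v 50%. The stratum results should therefore be read as estimates with intervals, with the adjusted pooled analysis carrying the test.

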### Interventions

We developed an early intervention for panic symptoms, called the 'Don't panic' course. The course is based on cognitive-behavioural principles and makes use of interventions that have appeared effective in the treatment of the full-blown disorder [27-29]. This intervention was developed specifically for adults. It consists of eight weekly sessions of two hours each in groups of six to 12 participants. The 'Don't panic' course makes use of a course manual [30], to be used by the psychologist and prevention worker offering the intervention, and an accompanying workbook for the participants [31]. The course instructors received a one-day training in offering the course and working with the course manual, to ensure integrity of the intervention delivery. Participants were taught to examine their panic attacks and the possible causes, to use techniques to influence their anxiety, and to develop skills to improve how they cope with panic attacks. The course includes (a) a psycho-educational element about the nature and physiology of anxiety and panic attacks, (b) life-style changes to improve physical condition, (c) stress management to prevent constant tension by learning effective ways to cope with stress, (d) relaxation training to reduce physiological arousal, (e) cognitive restructuring to challenge and correct dysfunctional cognitions of panic and anxiety, (f) interoceptive exposure to reduce the fear of somatic sensations, (g) 'in vivo' exposure to reduce agoraphobic avoidance, and (h) techniques aimed at relapse prevention. During the course the participants had to evaluate their progress. After three months following completion of the course a booster session was offered. Each session was structured to include a discussion of homework assignments, feedback, rehearsals, information about the upcoming topic and practical skills training. The intervention was extensively pilot-tested before entering the clinical trial stage.

The control condition consisted of a waiting list. Waitlisted people were told that they could start the course after four months. They were not kept waiting for the extended follow-up for ethical reasons.

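### Maintenance to T2 is tested by within-arm paired t tests of zero change, which cannot establish maintenance when non-significant and lack the clustering control promised for effectiveness analyses

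*Protocol article*

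**What the plan says.** The Analyses section names the method for durability: "To test the maintenance of the effects at six-month follow-up we used a paired-samples t test to analyze the difference in mean score". This applies to the self-report questionnaires, for each of the three pairings of T0, T1 and T2, and only within the intervention arm. There is no control arm in these contrasts. The article gives no margin, interval or other criterion for maintenance, and the section closes by applying a two-sided 0.05 level to every test.

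Earlier in the same section the article makes a general commitment: "In all analyses on effectiveness, we controlled for the clustering of data caused by the multi-site character of the study". Its stated reason is that clustered observations are not independent, which can distort both precision and P values, and it says that robust standard errors come from Taylor series linearization.

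On timing, Study design has baseline "followed by a posttest measurement after three months (T1") and places the last measurement "nine months after baseline, i.e., six months after the end of the intervention (T2"). Interventions describes the course, "It consists of eight weekly sessions of two hours each in groups of six to 12 participants", and adds: "After three months following completion of the course a booster session was offered".

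**The concern.** There are two statistical problems and one of wording.

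- **Test and claim do not match.** A test of zero change from T1 to T2 can reveal deterioration. If it is not significant, either the improvement was kept or the study was too imprecise to see the loss, and the test cannot tell these apart. The T0-T2 contrast shows only that scores differ from baseline, which a partly lost improvement would also show.
- **The named test does not follow the article's own rule.** An ordinary paired t test has no term for centre. As written, the maintenance analysis departs from the clustering control announced for all effectiveness analyses, and no exemption is stated.
- **The T2 label leaves out the booster.** The booster is described under Interventions and falls between T1 and T2, yet Study design dates T2 from the end of the intervention.

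T2 is the trial's only evidence on durability. What is at stake is whether a statement that effects lasted for six months rests on an estimate or on a lack of precision.

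**Working it through.** **Inputs from the article.** 129 per condition, standardized difference 0.35, two-sided alpha 0.05, power 0.80 (Sample size); T1 at 3 months and T2 at 9 months (Study design); course of eight weekly sessions and booster three months after completion (Interventions).

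**Assumed inputs.** The article gives no T1-T2 correlation r, no intraclass correlation, no number of centres and no T2 dropout. I take r from 0.5 to 0.81 and equal SDs at T1 and T2.

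**Step 1: the plan's own figure.** n per arm = 2 × (1.960 + 0.842)² / 0.35² = 15.70 / 0.1225 = 128.2, rounded up to 129. It reproduces. It is the size for the between-arm comparison and says nothing about maintenance.

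**Step 2: precision of the T1-T2 change.** In units of the score SD, the SD of the change is √(2(1 − r)). The 95% half-width is t × √(2(1 − r)) / √n, with t = 1.979 and √129 = 11.36.

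| r | SD of change | Half-width, n = 129 | n = 100 | n = 80 |
|---|---|---|---|---|
| 0.5 | 1.000 | 0.174 | 0.198 | 0.223 |
| 0.7 | 0.775 | 0.135 | 0.154 | 0.172 |
| 0.81 | 0.616 | 0.107 | 0.122 | 0.137 |

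For scale only, 0.107 / 0.35 = 31% and 0.174 / 0.35 = 50% of the planned between-arm difference. The columns for 100 and 80 show what fewer observed T2 scores would do. None of these widths allows for clustering.

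**Step 3: chance that a real loss is not significant (n = 129, noncentral t).**

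| True loss (SD) | r = 0.5 | r = 0.7 | r = 0.81 |
|---|---|---|---|
| 0.117 | 0.74 | 0.60 | 0.43 |
| 0.175 | 0.50 | 0.28 | 0.11 |

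The result depends strongly on r. The logical point does not: at any r some loss is compatible with a non-significant test, and only the interval shows how much.

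**Step 4: clustering.** If change scores within a centre have intraclass correlation ρ and centres contribute m participants each, the variance of the mean change is multiplied by about 1 + (m − 1)ρ. The relevant ρ is that of change scores, because stable differences between centres cancel in a paired difference. Neither m nor ρ is given, so no figure can be attached to this trial. If ρ is positive, the unadjusted standard error is too small. For T1-T2 that produces false alarms of change. For T0-T1 and T0-T2 it overstates the certainty of improvement over baseline.

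**Step 5: timeline.** If the course ends near T1, the booster falls at about 3 + 3 = 6 months and T2 follows 9 − 6 = 3 months later. If the course ends after eight weeks, about month 2, the booster falls at about month 5 and T2 follows about 4 months later. Either way the booster lies between T1 and T2.

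**The case against.** The strongest defence is that the analysis is modest and its main weakness is disclosed. Study design speaks of monitoring maintenance. Strengths and limitations concedes that there is no control at T2 and rules out definite attribution to the intervention. The article never says that a non-significant T1-T2 result will be read as maintenance, and a margin could sit in the full protocol. Much of this stands, and it limits the weight of the point. But the concession concerns causal attribution, not inference from non-significance or unadjusted standard errors. The article also does name the method by which maintenance is tested, so this is a stated choice and not an omission.

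A paired comparison can be run with linearized standard errors, and the general sentence on clustering may have been meant to cover it. That is possible, but the text names the ordinary test and does not say so.

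Three stronger readings are tempting, and the documents do not support them:

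- **That the trial would miss the loss of half its gain in 40 to 49% of cases.** This takes r = 0.5 to 0.6 and a loss of 0.175 SD. At r = 0.7 the figure is 28%, and at 0.81 it is 11%. Moreover, 0.35 SD is the planned difference between arms, not the within-arm improvement, which the article does not give.
- **That ignoring clustering gives a type I error of 7 to 14% and so false claims of maintenance.** Those figures are for course groups of 9 with assumed intraclass correlations of 0.02 to 0.10. The article promises control for centres only, not course groups. For T1-T2 the error would also run towards declaring change, not towards declaring maintenance.
- **That the booster is concealed or the T2 result is wrongly credited to the eight sessions.** The booster is openly described, and Strengths and limitations dates follow-up from the end of the course. Only the phrase in Study design is loose.

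**Conclusion.** The point holds in a limited form. Within-arm tests of zero change are named as the test of maintenance, and a non-significant T1-T2 result would not establish it. With 129 participants the 95% half-width is about 0.11 to 0.17 SD for an assumed correlation of 0.81 to 0.5, before any allowance for clustering, and it is wider if fewer are measured at T2. The named test also lacks the centre-clustering control that the article says applies to all effectiveness analyses. The effect of that cannot be quantified from the article, because it depends on the intraclass correlation of change scores. The booster is a matter of wording. This is a secondary, single-arm analysis, and the primary between-arm comparison at T1 is untouched.

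**What to change.** 1. Replace the paired t tests by a regression or mixed model for T0, T1 and T2 in the intervention arm, with the same linearized, cluster-robust standard errors as the other effectiveness analyses. A regression of each change score on a constant, with centre as the cluster, would be enough.
2. Report the T0-T1, T0-T2 and T1-T2 changes as estimates, and the T1-T2 change with its 95% confidence interval. Do not conclude maintenance from non-significance. State instead what size of loss the interval excludes.
3. Reconcile Study design with Interventions, so that T2 is placed relative to both the last weekly session and the booster, and describe T2 results as following the course plus the offer of a booster.

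This changes analysis and wording only and needs no new data. Recording booster attendance would be data collection and is not part of the fix. The downside is that a claim of maintenance becomes harder to make.
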